#### Upper respiratory tract infection (URTI)

As exacerbations, URTIs are identified from participants’ diary, from 3-months retrospective questionnaires completed at all clinic visits, from interviews at study visits and from telephone contacts. URTI are defined as at least 3 consecutive days of runny nose and sore throat.

#### Courses of unscheduled antibiotics

Antibiotic use is documented at all clinic and study visits as well as in participants’ diaries and antibiotics courses (intravenous, oral or inhaled) are counted. In case of exacerbation, planned study visits are postponed until 14 days after oral or intravenous antibiotic treatment of exacerbation has been stopped.

### Substudies

#### Accelerometry

In European countries, PA is assessed by an accelerometer (Actigraph GT1M or wGT3X, Pensacola, FL, USA), which is worn at the right hip over 7 days at baseline and prior to the 6 and 12-months study visits. The sampling epoch is set at 5 s and data are included if at least 4 full days (at least 3 weekdays and one weekend day) of measurements with a minimum of 10 h for the weekdays and 10 h for the weekends are measured [26]. Overall PA is expressed as average counts/min and time (min/day) in light, moderate and vigorous PA according to validated cut-off levels [27–29].

#### Multiple breath washout

Lung clearance index is determined using commercially available systems based on nitrogen washout (EasyOnePro Lab, ndd Medical Technologies, Zurich, Switzerland; ECO MEDICS AG, Dürnten, Switzerland) in centres with access to this or similar technology. Measurements are performed prior to spirometry and body plethysmography following the manufacturers’ instructions. The methodology has proven to be feasible in multi-centre trials [30].

#### Dual energy X-ray absorptiometry

Body composition and bone parameters are measured using dual-energy X-ray absorptiometry in Canadian and Swiss participants. Body composition is assessed by the three-compartment model, including fat mass, bone mineral content, and bone mineral free lean tissue. Bone mineral content and bone mineral density values are z-transformed using pubertal stage- and gender-specific means and standard deviations [31].

#### Mucociliary clearance

Mucociliary clearance (MCC) is measured using nuclear medicine scans at baseline (visit 1a), immediately after a submaximal exercise test (visit 1b), and then prior to their maximal CPET at patient’s 6-month study visit, to investigate the acute effects of exercise and the effects of increased activity and vigorous PA over a 6-month period on mucociliary clearance.

### Monitoring and quality assurance

Standard operational procedures (SOP) for all the methods used in the study are available in English. Moreover, essential parts of the SOPs are translated in all national languages of participating countries. A site initiation visit takes place at each center prior to the enrolment of the first patient in the study. A close out visit takes place when the last study participant at each center has completed the study.

Central data monitoring of REDCap database entries and on site monitoring are done for the majority of database entries, especially inclusion and exclusion criteria and study outcomes including safety data to assure high quality data. In particular, all lung function data entries and pseudonymized pulmonary function reports (primary endpoint FEV_1_) are checked for accuracy and correctness according to ATS/ERS standards [14, 15].

A close out visit takes place when the last study participant at each center has completed the study.

### Data safety monitoring board (DSMB)

For this study a DSMB Safety Board was implemented. Each serious safety issue is reported to the Board within 72 h. The safety board can request an interim analysis and can stop the study in case of serious safety issues.

### Statistical analysis

Descriptive analyses using means and standard deviations, medians and interquartile ranges or means and 95% confidence intervals (CI’s) will be used for continuous variables as appropriate. Frequencies and proportions with 95% CI’s will be used for categorical variables. Primary analyses will be performed according to intention-to-treat (ITT) with all participants who were originally allocated by randomisation and those who dropped out from the study. ITT main analysis and analyses on secondary outpoints will be done including missing data imputations by multiple imputation, inverse probability weighing or mixed models as appropriate.

Additionally, we will perform sensitivity analyses using the per protocol set and run analyses based on *reported* and *assumed* compliance. The analysis of reported compliance will include all patients sufficiently compliant with the protocol and include those randomised into the intervention group with the addition of at least 2/3 of training volume (e.g., the addition of 2 h per week of vigorous PA) and compare to those randomised into the control group with no more than 30 min of extra vigorous PA per week during the period of interest than at baseline. The analysis on assumed compliance will include those from the intervention group with an increase of 5% and more of VO_2peak_ from baseline as marker of compliance with the programme and compare to those randomised into the control group with less than 5% increase of VO_2peak_ from baseline as marker of compliance with restraining from training.

The secondary efficacy endpoints will be analysed according to the main model described above. This includes the 0 to 6 months and the 0 to 12 months’ time periods for most variables, and the effects of the intervention on the change in FEV_1_ over 12 months, and the change in FEV_1_ between month 6 and month 12. Likewise, the change in glucose levels 1 and 2 h after a standardised glucose load between baseline and 9 months will be compared between groups. The endpoint “time to first exacerbation” will be analysed using a Cox proportional hazard model, while Poisson regression will be used for “number of upper respiratory tract infections”. The frequency of study participants developing diabetes mellitus between baseline assessments and 9-months follow-up will be compared between groups using chi square statistics. For safety endpoints, data will be monitored throughout the study for all patients. Analysis will be performed on total number of events and type of event (fracture, sprain, hypoglycaemia, haemoptysis, pneumothorax, etc.). The change from 6 to 12 months for all secondary outcomes and for the other explorative endpoints will be analysed with the main model described above except for “days on oral / intravenous antibiotics” which will be analysed using Poisson regression.

For the main analysis, the statistician and the PI will have full access to the dataset including the DSMB. Later, for secondary analysis, data will be shared among national coordinators.

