### Study endpoints and measurements

The primary outcome measure is the difference between the changes in FEV_1_ (in % predicted) from baseline (using the average of the two baseline measurements) to 6 months in the intervention group compared to controls. Secondary outcomes include change in aerobic exercise capacity (VO_2_peak), PA, HRQoL and others listed in Table 2. Vital signs, anthropometric characteristics (weight, height, skinfolds) are measured at each study visit using standardised procedures.

**Table 2 Tab2:** Primary, secondary and explorative outcome measures

Outcome	Variable	Measurement
Primary endpoint		
• Lung function	FEV_1_% predicted	Spirometry
Secondary endpoints		
• Exercise capacity	VO_2peak_ % predicted	CPET
	Watt_max_ % predicted	CPET
• Physical activity	Steps per day	Pedometry
	Exercise steps per day	Pedometry
	Reported physical activity (min per day)	7-day recall questionnaire
• Pulmonary function	FEV_1_% predicted	Spirometry, Bodyplethysmography
	FVC % predicted	
	RV/TLC %	
• Exacerbation	Time to first exacerbation	Questionnaire (modified Fuchs criteria) and physician assessment
• Body composition	Body fat	Skinfolds
	Lean body mass	Skinfolds
• Health-related quality of life	Scales	Questionnaire (CFQ-R)
• Depression, anxiety and stress scales	Scales	Questionnaire (DASS)
• Glycaemic control	Plasma glucose concentrations (fasting, 1 and 2 h after standardised glucose load)	Oral glucose tolerance test^a^
Explorative endpoints		
• Physical activity	Moderate and vigorous physical activity	Accelerometry^b^
• Infections	Number of upper respiratory tract infections	3-months retrospective questionnaire, Interviews, Diary and telephone calls
• Antibiotic therapy	Days on additional oral/intravenous antibiotics	3-months retrospective questionnaire, Interviews, Diary and telephone calls
• Body composition	Body mass index	Based on measured height and weight
• Lung function	Lung clearance index	Multiple breath washout^c^
• Mucociliary clearance	Mucociliary clearance	Scintigraphy^d^
Safety endpoints		
• Adverse events	Adverse events at least possibly related to exercise (e.g., sprains, fractures etc)	Judged by investigator
Others		
• Compliance with exercise	Exercise goal of 3 additional hours of vigorous activity per week	Baseline assessment and web-based diary

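### The two compliance comparisons select on post-randomisation variables in opposite directions by arm, so they can show an FEV1 benefit when the programme has none and cannot test the ITT result

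*Protocol article*

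**What the plan says.** The Statistical analysis section of the protocol article makes ITT primary: "Primary analyses will be performed according to intention-to-treat (ITT) with all participants who were originally allocated by randomisation". It continues: "Additionally, we will perform sensitivity analyses using the per protocol set and run analyses based on" reported and assumed compliance.

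- **Assumed compliance** keeps "those from the intervention group with an increase of 5% and more of VO_2peak_ from baseline as marker of compliance with the programme" and compares them with "those randomised into the control group with less than 5% increase of VO_2peak_ from baseline as marker of compliance with restraining from training".
- **Reported compliance** keeps "those randomised into the intervention group with the addition of at least 2/3 of training volume" (2 h per week is the example given) and compares them with "those randomised into the control group with no more than 30 min of extra vigorous PA per week".

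VO2peak is also an efficacy outcome: "Secondary outcomes include change in aerobic exercise capacity (VO_2_peak), PA, HRQoL and others listed in Table 2". Table 1 places the exercise test and spirometry at the same 6-month visit. The section states no adjustment for the selection.

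**The concern.** Both rules condition on something observed after allocation, and they keep opposite sides in the two arms. A VO2peak rise of 6% admits a patient in the intervention arm and removes the same kind of patient from the control arm. The reported-compliance rule also drops everyone between the two cuts. The groups compared are therefore no longer those that randomisation made alike.

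If patients whose VO2peak or activity rises also tend to have a better FEV1 course, for any reason unrelated to allocation, the rule gathers better FEV1 changes in one group and worse ones in the other. The contrast then favours the intervention without any programme effect on FEV1. Placed beside the ITT result, such a contrast could be taken as support for a positive finding or as a reason to discount a null one. It can do neither job.

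**Working it through.** **Inputs from the protocol article (Sample size calculation):** design difference 3% predicted, SD of FEV1 change 8, power 80%, type 1 error 5% (two-sided assumed), dropout 20%, 292 patients, 1:1 allocation.

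**Design figure first.** A two-sample t-test with difference 3 and SD 8 needs 113 per arm. Then 113/0.8 = 141.25, so 142 per arm and 284 in total, close to the stated 292. With 292 × 0.8 / 2 = 116.8 completers per arm, power is about 81%. The inputs are consistent with 292, and about 117 completers per arm is used below. (The section also gives 202 once. Power would then be about 66%, so 292 is the figure that fits.)

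**Inputs assumed, because the protocol does not give them:** the within-arm correlation r between the selection variable and FEV1 change; VO2peak change with mean 0 and SD 12, in the units of the 5% threshold; bivariate normality; no programme effect on FEV1.

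**Formula.** With c_int and c_ctl the standardised cuts in the two arms,

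bias = r × 8 × [φ(c_int)/(1 − Φ(c_int)) + φ(c_ctl)/Φ(c_ctl)].

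**Assumed compliance, same VO2peak distribution in both arms.** c = 5/12 = 0.417, φ(c) = 0.366, Φ(c) = 0.662. The bracket is 0.366/0.338 + 0.366/0.662 = 1.08 + 0.55 = 1.63. The bias is r × 8 × 1.634 = 13.07r. About 34% of the intervention arm and 66% of controls are kept.

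| r | Spurious FEV1 difference | Rejection rate, nominal 5% test (5,000 simulated trials) |
|---|---|---|
| 0 | 0 | 5% |
| 0.1 | 1.3 | 14% |
| 0.2 | 2.6 | 38% |
| 0.3 | 3.9 | 72% |
| 0.4 | 5.2 | 94% |

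The all-patient comparison of the same simulated data rejects about 5% of the time throughout. A spurious difference equal to the 3-point design effect needs r = 3/13.07 = 0.23.

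**Sensitivity to the assumed VO2peak distribution**

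- SD 10, 15 or 20 with mean 0: 1.32, 1.30 or 1.29 points per 0.1 of r.
- Mean −2, SD 12: 1.34 points per 0.1 of r.
- Programme raises VO2peak by 5 (c_int = 0): bracket 0.80 + 0.55 = 1.35, so 3.2 points at r = 0.3 and 2.2 at r = 0.2.
- Programme raises VO2peak by 10 (c_int = −5/12): bracket 0.55 + 0.55 = 1.11, so 2.7 points at r = 0.3 and 1.8 at r = 0.2.

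**Reported compliance.** Assume extra vigorous activity has mean 0 and SD 2 h per week in both arms. Then c_int = 2/2 = 1 and c_ctl = 0.5/2 = 0.25. The bracket is 1.53 + 0.65 = 2.17, so the bias is 1.7 points per 0.1 of r, or 3.5 at r = 0.2. Over four assumed activity distributions, two of which let the programme raise activity by 1.5 or 2 h per week, the bias at r = 0.2 runs from 2.2 to 3.7 points.

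**The case against.** **The primary inference is not at risk.** This stands. ITT on all randomised patients is fixed as primary, and nothing lets the compliance comparisons override it. A reader might infer that the trial's main conclusion is compromised; the text does not support that.

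**The bias is conditional.** This also stands. At r = 0 the contrast is zero and the test holds its 5% level. A reader might infer that these analyses must produce a benefit under a null programme, but the protocol gives no correlation. Its Discussion cites observational work linking regular activity to slower FEV1 decline. That suggests a positive sign, but it concerns activity rather than VO2peak and gives no size. That shared health status moves both measures at one visit is an assumption too, and postponing visits until 14 days after exacerbation antibiotics end would lessen it.

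**The programme probably raises VO2peak.** The Discussion calls effects on aerobic capacity largely consistent. The bias is then smaller, as the working shows, but it does not vanish.

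**The sensitivity label is unclear.** In the sentence that introduces these analyses, the word attaches plainly to the per protocol set and only arguably to the compliance comparisons. It would be too strong to say that the protocol labels both as sensitivity analyses.

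**Reported activity is a behaviour, not a response.** True, but it is still observed after randomisation and cut in opposite directions. A reader might also infer from the Table 2 compliance source, "Baseline assessment and web-based diary", that activity must be measured differently by arm, since only the intervention group keeps the web diary. That row concerns the 3-hour exercise goal, and Table 1 schedules the 7-day recall for both arms at every visit, so a difference in measurement is not established.

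**Conclusion.** The concern holds in conditional form. Both rules select in opposite directions by arm on post-randomisation variables, and with any positive within-arm correlation with FEV1 change they favour the intervention when FEV1 is unaffected. For the VO2peak rule the size is about 1.3 points per 0.1 of correlation, so a correlation near 0.23 would match the 3-point design effect. If the programme raises VO2peak by 5 or 10, the bias at a correlation of 0.3 is about 3.2 or 2.7 points instead of 3.9.

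These figures rest on the protocol's SD of 8 and on an assumed correlation, an assumed VO2peak distribution and normality; the correlation drives the result and the VO2peak SD hardly matters. The documents do not show that the bias will occur or how large it will be. They do show rules under which these contrasts cannot test the robustness of the ITT result or support efficacy. This should be fixed, but it does not threaten the primary analysis.

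**What to change.** In the Statistical analysis section, state that both compliance comparisons are descriptive and non-randomised, that they carry no significance test, and that they are not sensitivity analyses of the primary result.

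If an effect of adherence is wanted, keep all randomised patients and use allocation as the instrument for the change in vigorous activity from the 7-day recall. Enter that change as a continuous exposure: with a compliance cut, a patient who adds 1.5 h per week counts as a non-complier yet may still benefit. State the exclusion restriction, namely that allocation affects FEV1 only through vigorous activity. Counselling, phone calls and the pedometer are part of the programme and could work in other ways, so this needs an argument.

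The cost is a few sentences and one model on data already scheduled. The downside is a wider confidence interval and reliance on that restriction.

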## Discussion

This is the first large international randomised controlled trial to study the effects of regular vigorous PA with motivational feedback on important clinical, physiological and patient-reported outcomes in CF. Previous exercise training studies in CF were mostly of low to moderate methodological quality with small numbers of patients and conducted over short periods of time [3]. While the positive effects of exercise training and PA interventions on aerobic exercise capacity are predominantly consistent among studies, the effects on HRQoL and pulmonary function including FEV_1_ are less clear [3]. Two supervised exercise interventions demonstrated that regular vigorous exercise has the potential to positively impact FEV_1_ [4, 5]. These data are supported by observational studies, showing that regular PA is associated with a slower progression of FEV_1_ decline over time [32, 33]. Despite the limitations of FEV_1_ as clinical endpoint [34], FEV_1_ is the most commonly used endpoint in clinical trials and still the single best prognostic factor for CF [6]. The main aim of our study is to evaluate whether regular vigorous habitual PA can prevent deterioration of FEV_1_ decline over time that is much more clinically relevant than to demonstrate short-term improvements.

Our secondary aim is to study other important endpoints such as bone health, pulmonary exacerbations, glycaemia control and patient-reported outcomes such as HRQoL, depression and anxiety that have been rarely investigated in exercise training and PA interventions in CF [3]. Some of these endpoints have been previously investigated in cross-sectional, observational and/or small randomised controlled trials showing some beneficial effects of PA on bone health [35], glycaemic control [36] and hospitalisation days [33], but these data need to be further substantiated by a large randomised controlled study and ideally including patients with a broad age range and disease severity to be representative for the overall CF population. The focus of patient-reported outcomes is very important and in the past has been often neglected in trials.

A critical point in each PA intervention study especially in chronic disease is adherence and compliance of the patients. Using pedometers to provide feedback on daily PA can enhance motivation to exercise [37] and has been shown to be effective in activity programs addressing people with a variety of chronic health conditions (10) including youth [38] and patients with chronic obstructive pulmonary disease [39]. Providing additional feedback on exercise behaviour by keeping a diary as well as giving personal feedback via a SMS message to the cellular phone, email or telephone also enhanced adherence to a home-based exercise programme that was partially supervised [40, 41].

The major strength of the current investigation is the inclusion of a heterogeneous study population with a broad range of disease severity (FEV_1_ ≥ 35% predicted) and recruited from eight different countries in Europe and Northern America. The use of modern technology (step counters and web-based diary) for PA monitoring is unique to exercise studies in this patient population and will provide new insights into the usefulness and feasibility of these wearables.

### Limitations

Due to the nature of a partially supervised study, adherence to PA and data entries in the web-based diary cannot be fully controlled. However, objective measures of exercise capacity using CPET and PA (substudy using Actigraph accelerometry) will be used to verify training effects after 6 and 12-months and will provide an indication of whether study participants adhered to their training schedule or not. Blinding of study participants to minimise bias is not possible in PA intervention studies, but outcome assessors are blinded, whenever possible. A selection bias towards a physically active CF population may occur, because patients who are physically active in their daily lives might be more likely to participate in this trial.

Patient recruitment for long-term PA interventions is challenging [5], in particular in rare diseases such as CF. Moreover, there are several recent drug trials on the effects of CF transmembrane conductance regulator corrector and potentiator therapy that might interfere with the ACTIVATE-CF trial. Major efforts have been done with respect to study center recruitment. The study is currently running in > 20 specialised CF centers in eight countries in Europe and Northern America. The first study participant was enrolled in June 2014 and the last study participant is expected to complete the last study visit in June 2018.

This study could make an important contribution to the knowledge on the effects of regular vigorous PA on several important health outcomes in CF. In particular, the use of modern PA monitoring and motivational feedback embedded in the intervention will enhance our understanding on the feasibility and usefulness of these tools with respect to long-term PA adherence.

## Abbreviations

CF: Cystic fibrosis
CFQ-R: Cystic fibrosis questionnaire-revised
CFRD: Cystic fibrosis related diabetes
CI: Confidence interval
CPET: Cardiopulmonary exercise testing
DASS: Depression anxiety stress scales
DSMB: Data safety monitoring board
eCRF: electronic Case Report Form
FEV_1_: Forced expiratory volume in 1 s
FVC: Forced vital capacity
HRQoL: Health-related quality of life
ITT: Intention-to-treat
MCC: Mucociliary clearance
PA: Physical activity
SOP: Standard operating procedure
URTI: Upper respiratory tract infection
VO_2_peak: Peak oxygen uptake
Watt_max_: Maximal aerobic power
